## Assignment of interventions: allocation

### Sequence generation {16a}

After baseline assessment, randomization will be 1:1 stratified by study center, patient age (< 81 years vs. ≥ 81 years), and gender (block randomization with random block lengths). Randomization will be performed by unblinded study physicians at the recruiting centers. After randomization, the patient will be informed about the respective allocation. In case of allocation into the intervention group, the prehabilitation center will be contacted by the unblinded study physician. The individual outcome assessors at the recruiting centers remain blinded.

### Concealment mechanism {16b}

Participants will be randomized using secuTrial®, the electronic database for the pseudonymized data management of the PRECOVERY trial. Allocation concealment will be ensured, because the unblinded trial physician will not press the button for allocation until the patient has been recruited into the trial. The baseline assessments will be completed by an outcome assessor who is blinded to the allocation of the patient in intervention or SMC group.

### Implementation {16c}

The allocation order is determined by the Institute of Medical Statistics of the University Medical Center Goettingen, Germany.

## Assignment of interventions: blinding

### Who will be blinded {17a}

Due to the nature of the intervention, all participants and staff members in the prehabilitation centers cannot be blinded. Therefore, blinding to group allocation will be limited to outcome assessors.

### Procedure for unblinding if needed {17b}

In the recruiting centers, the outcome assessors are determined to be the blinded study personnel. Once unblinded, outcome assessors cannot perform tasks that require blinding. Unblinding must be reported in the deviation log, in the secuTrial® database as well as for the recruiting center in a correspondingly suitable place, e.g., assignment list.

## Data collection and management

### Plans for assessment and collection of outcomes {18a}

The various assessments to be applied in the different data collection dates are shown in Table 4 and in the translated approved study protocol [Additional file 1].

The medical history includes age, height, weight, hip to waist ratio, blood pressure, heart rate, cardiovascular risk factors, and other cardiac and non-cardiac conditions. Previous cardiac and vascular surgical procedures will be also documented. Sociodemographic data will be included in the database in the form of marital status and education level, among others. Routine laboratory chemistry data before and after the cardiac procedures will be incorporated into a standardized laboratory protocol. Furthermore, we will complete a cardiac surgery or cardiac intervention protocol detailing the cardiac procedure. The total length of inpatient stay, the length of stay in the intensive care unit, and the performance as well as duration of cardiac rehabilitation will be recorded. Likewise, before and after the cardiac procedure, the occurrence of dyspnea will be documented. Postoperative/postinterventional complications (e.g., hemorrhage, pleural effusions, pneumothorax, cardiac arrhythmias) as well as mortality after 30 days and 1-year are systematically recorded. In order not to overlook the occurrence of delirium, the patient record is reviewed. If there are signs of severe agitation or other delirious symptoms according to ICD-10, the patient is classified as delirious. All peri- and postoperative data will be collected from the hospital electronic database or routine clinical documentation.

General QoL will be assessed by EQ-5D-5L [24] and disease-specific QoL by HeartQol [30, 64].

Functional assessments include the SPPB [27, 65], 6-min walk test [37], and handgrip strength [35, 36]. Daily activity will be measured by Katz Index [25, 26].

Frailty will be identified with the CFS [48], the Mini Nutritional Assessment [39, 40], and in a subgroup analysis by Bioelectrical Impedance Analysis [38].

Cognitive function will be screened with MoCa [28, 29, 66], SMI [50], and IQCODE [46].

Psychosocial assessments include the HADS [31–33], Pittsburgh Sleep Quality Index [41–43], Maastricht Questionnaire [44, 45], SWE scale [51, 52], LOT-R [55], UCLA Loneliness Scale [56, 57], IPQ [58], and TEX-Q [59].

A modified version of the Hamburg Questionnaire on Hospital Stay will be assessed after the cardiac procedure, and G-ZBI will be used to measure the burden relatives experience during the perioperative time [47].

Healthcare costs will be collected using the FIMA questionnaire [34] in combination with routine data from the AOK (health insurance data).

Adherence to the prehabilitation program is monitored through documentation of each session created by the process evaluation team. A patient diary is completed by the patient after each session in order to evaluate patient performance afterwards.

All data collected in paper form are documented in secuTrial® (eCRF) by the outcome assessors immediately after the survey. Data entry is based on the 4-eye principle—each entry is checked again by another person.

Finally, optional blood samples will be collected and analyzed on four data collection dates to examine neurodegenerative, inflammatory, cardiac, genomic, and epigenetic markers, approximately 50 ml each.

For the process evaluation, quantitative data will be collected in standardized interviews with patients, their relatives, and professionals involved in the prehabilitation. Further data will be collected via patient diaries and therapy plans. In addition, qualitative data (interviews and focus groups) will be gathered to take into account the perspectives of patients and professionals involved in the prehabilitation process. The goal is to better understand the implementation of the intervention and its consequences.

All principle investigators, outcome assessors (1 day), and prehabilitation center multipliers (2 days) will receive an intensive training prior to enrollment of the first patient.

### Plans to promote participant retention and complete follow-up {18b}

In order to strengthen participant retention, e.g., travel costs for the journey to prehabilitation and back home as well as to t6, the last survey, are covered. At the individual survey times, patients also receive examinations outside of routine care, which can help to detect abnormalities at an early stage. To emphasize that, the outcome assessors point this out at the survey times to promote compliance.

### Data management {19}

Details on data management are described in detail in a data management plan. Assessments are recorded on paper and data are entered remotely via an electronic case report form (eCRF) and stored pseudonymously in a provided secuTrial® database, an established GCP-compliant web solution. The secuTrial® data entry screens resemble the paper forms used. Blinded outcome assessors enter data in the secuTrial® database. This data is confirmed by a second person in an independent step.

### Confidentiality {27}

The data for the evaluation stored in the secuTrial® are made available to the evaluating institutions via encrypted email program (e.g., Cryptshare). In addition to the data from the eCRF, pseudonymized routine data from the AOK are also made available for the health economic evaluation. These data are transmitted to the evaluating institution via a secure connection. The identification of the study participants at the health insurance companies is done via the insurance number, which is collected when the patients are enrolled in the study and transmitted to the respective AOK together with the study ID. The original paper-based completed questionnaires will be stored securely and destroyed after 10 years in accordance with the legal conditions of data protection.

### Plans for collection, laboratory evaluation, and storage of biological specimens for genetic or molecular analysis in this trial/future use {33}

In case if participants voluntarily consented to the supplemental study up to 50 ml of blood will be collected per visit (t0/t1, t2, t3, t6) and stored as cellular as well as non-cellular components. The focus is to detect neurodegenerative, inflammatory, and cardiac markers, genomic and epigenetic markers (e.g., ApoE-Genotyps) out of these biospecimens. The processing and storage of biospecimens (serum, plasma, RNA from PAXgene tubes) will be performed according to locally established SOPs. This is a multicenter study, thus blood samples will be collected using identical SOPs for processing and intermediate storage at different study sites. Finally, samples will be shared, exchanged, and analyzed under a common agreement. This means that the blood samples and medical data collected will first be stored, analyzed, and used at all study sites within the project. Because the blood-based biomarkers are valuable data and samples that will be of great value for research, there are no plans to destroy the samples. If a patient withdraws from study participation, he/she may decide whether biospecimens that have already been stored may either be anonymized, may be further used or must be destroyed and data deleted.

## Statistical methods

### Statistical methods for primary and secondary outcomes {20a}

Details on statistical analysis are described in a statistical analysis plan (see Additional file 2). The primary endpoint EQ-5D-5L will be evaluated using a joint model for longitudinal data. Stratification factors of age, sex, participation in DMPs, and center will be included as covariates in the model. Time courses of EQ-5D-5L are presented longitudinally for each group, and survival rates are presented descriptively using Kaplan–Meier curves. Treatment effects are reported with 95% confidence intervals. The secondary endpoint HeartQoL is evaluated analogously to the primary endpoint. Secondary endpoints Katz Index, SPPB, MoCa, and HADS are evaluated using mixed linear models, with the factors time point, treatment, and the interaction, and the covariates age, sex, DMP participation, and center. Marginal means are calculated for inter- and intra-group comparisons, and treatment effects are reported with 95% confidence intervals. Likewise, for the analysis of the health economic outcomes, mean differences are calculated in mixed regression models. Because of the skewed distribution of the cost data, the non-parametric bootstrapping procedure, which is also used in the uncertainty analysis of the incremental cost-effectiveness ratio (ICER), is additionally used to calculate the standard errors of the regression parameters. For the analysis of cost-effectiveness, the net-benefit regression procedure is used. Details can be found in the Additional file 1 “Study Protocol”.

Statistical methods in the process evaluation:

For the process evaluation, exploratory sensitivity analyses will be performed to assess the impact of dose, reach, fidelity, and adaption on the intervention’s efficacy. For this purpose, interaction-terms between the treatment variables and these factors will be included in the mixed linear models described above. In addition to the intention-to-treat population, a population will be defined that started the intervention as intended and stays adherent during the follow-up period (starting and adhering estimand).

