### Participant timeline {13}

Table 4 summarizes the schedule of enrolment, intervention, and assessments in the PRECOVERY trial.

**Table 4 Tab4:** Schedule of enrolment, intervention, and assessments in the PRECOVERY trial

Time point	t0 (Screening)	t1 (Randomization/ Baseline)	t2 (Before CP)	t3 (After CP)	t4 (30 days after CP)	t5 (6 months after CP)	T6 (12 months after CP)
Inclusion/Exclusion criteria	x						
Informed consent, enrollment, allocation	x						
Medical history, social demographics		x					

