### Sample size {14}

A total number of 422 patients is planned for this intervention trial. The number of cases was planned on a confirmatory basis in order to be able to answer the primary questions with a power of 80%. A total of 338 patients (169 per treatment group) is sufficient to show a clinically relevant difference of 0.045 points in EQ-5D-5L at t6 with 80% power at the generally accepted two-sided significance level of 5%. It is assumed that the common standard deviation of the EQ-5D-5L is 0.17 and that the observations on the covariates have an R-squared of 0.25. Since this is a longitudinal study, a dropout rate of up to 20% is assumed, so a total of 422 patients will be recruited. The case number calculation was performed in nQuery version 8. The definition of a clinically relevant difference of 0.045 was based on the publication of McClure et al. [62], who restricted a minimal clinically relevant difference to values between 0.037 and 0.069 [62]. Since the publication did not include results on the German population, a value was chosen that was approximately 10% lower than the average of the countries considered in the publication. The assumption of a standard deviation of 0.17 is based on observations by [63], who observed a standard deviation of 0.171 at baseline and a standard deviation of 0.170 at 12-month follow-up in a sample of 1927 diabetes-2 patients [63].

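### The model sentence calls DMP participation a stratification factor and omits baseline EQ-5D-5L, while the 80% power is conditional on an unsourced covariate R-squared of 0.25

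*Protocol article*

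**What the plan says.** **Model.** Under Statistical methods for primary and secondary outcomes {20a}, EQ-5D-5L is analysed with a joint longitudinal model, and "Stratification factors of age, sex, participation in DMPs, and center will be included as covariates in the model". HeartQoL is handled in the same way. Katz, SPPB, MoCa and HADS get linear mixed models with time point, treatment and their interaction, plus the same four covariates. No baseline score is named in any of these lists.

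**Randomisation.** Sequence generation {16a} says that "randomization will be 1:1 stratified by study center, patient age" (<81 or ≥81 years) and gender. Trial design {8} names the same three factors: hospital, age and gender. DMP participation appears in neither place.

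**Sample size {14}.** "A total of 338 patients (169 per treatment group) is sufficient to show a clinically relevant difference of 0.045 points" at t6, with 80% power at a two-sided 5% level. "It is assumed that the common standard deviation of the EQ-5D-5L is 0.17", and further "that the observations on the covariates have an R-squared of 0.25". The section gives a source for the difference and for the SD. It gives none for the R-squared and does not name the covariates.

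**Baseline data.** Table 4 schedules EQ-5D-5L from t1 to t6, and section {20c} requires baseline values for a participant to be included in the analysis.

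**The concern.** Two things in the model sentence look wrong. First, it misdescribes the randomisation: DMP participation is called a stratification factor but was not one. DMP is not in the abbreviation list and is not a named item in Table 4 or among the baseline data in section {18a}.

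Second, the score measured before treatment is missing from a covariate list that is spelled out. The sample size assumes that covariates explain a quarter of the variance of 12-month EQ-5D-5L, which is a multiple correlation of √0.25 = 0.5. The article offers nothing to show that age, sex, DMP participation and centre reach that.

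At stake is the precision of the t6 comparison. If the model takes no variance reduction from baseline, chance imbalance in baseline quality of life stays in the effect estimate, and the power depends on whatever the four listed covariates happen to explain.

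**Working it through.** **1. Inputs (Sample size {14}).** Difference δ = 0.045; SD σ = 0.17; two-sided α = 0.05; power 80%; R² = 0.25; dropout 20%.

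**2. The plan's own figure.** Residual SD = 0.17 × √(1 − 0.25) = 0.1472.

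n per arm = 2 × (1.960 + 0.842)² × 0.1472² / 0.045² ≈ 168.03, rounded up to 169, so 338 in total. The noncentral-t calculation also gives 169, with power 80.0%. Dropout: 338 / 0.80 = 422.5, against 422 stated. The sample size reproduces, apart from rounding 422.5 down.

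**3. Dependence on R².** The article gives no R² for the listed covariates, so the values below 0.25 are assumptions. Residual SD = 0.17 × √(1 − R²). Power and required size are from the noncentral t.

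| R² | Residual SD | Power at 169 per arm | n per arm for 80% | Total evaluable | Recruited at 20% dropout |
|---|---|---|---|---|---|
| 0.25 | 0.1472 | 80.0% | 169 | 338 | 423 |
| 0.20 | 0.1521 | 77.4% | 181 | 362 | 453 |
| 0.15 | 0.1567 | 74.9% | 192 | 384 | 480 |
| 0.10 | 0.1613 | 72.5% | 203 | 406 | 508 |
| 0.05 | 0.1657 | 70.2% | 214 | 428 | 535 |
| 0 | 0.1700 | 68.0% | 225 | 450 | 563 |

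The assumed R² accounts for the whole reduction from 450 to 338 evaluable patients.

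**4. What baseline contributes under each form of model.** Take complete data, equal SD σ at t1 and t6, correlation ρ between them and n per arm. The variance of the between-arm difference at t6 is:

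- t1 as a response, with arm means free at every visit (ordinary time-by-treatment interaction): 2σ²/n, ratio 1.00 to the raw t6 comparison.
- Change from baseline: 2 × 2σ²(1 − ρ)/n. At ρ = 0.5 the ratio is 2 × 0.5 = 1.00.
- Baseline as covariate, or t1 as a response with equal means across arms: 2σ²(1 − ρ²)/n. At ρ = 0.5 the ratio is 1 − 0.25 = 0.75.

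The value ρ = 0.5 is an assumption; the article states no correlation. Having t1 in the longitudinal data is therefore not enough by itself. The gain at t6 needs a baseline covariate or a common-baseline constraint.

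**5. Randomisation against model.** Sections {8} and {16a} agree on centre, age and gender. Section {20a} adds DMP participation to the stratification factors. These statements cannot all be right.

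**The case against.** The strongest reply is that a baseline score which is not named need not be unused. The primary analysis is longitudinal, t1 is one of the EQ-5D-5L visits, and baseline values are required for inclusion. The score could enter as a covariate, as a free response or as a constrained one. The covariate sentence does not say that nothing else enters, and the article sends details to an analysis plan and a full protocol that were not available for this review.

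This stands in part: the article does not show that the primary model ignores baseline. It does not remove the point. The article chose to list the covariates, and the list carries a wrong label and leaves the score out. Of the ways t1 could enter as a response, the unconstrained one gains nothing at t6 in complete data. The models for Katz, SPPB, MoCa and HADS are stated with a time-by-treatment interaction and no constraint or baseline covariate.

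It is also fair to say that DMP participation explains the same variance whether or not it was used to stratify. The wrong label is a separate error and has no bearing on power. Nor does its absence from the named baseline items prove that DMP is not recorded, since the lists in section {18a} are open-ended.

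**Conclusion.** The point holds as two linked corrections. The model sentence contradicts the randomisation sections on DMP participation, and it omits a baseline score that the trial already collects. The sample size rests on an R-squared with no source and no named covariates. Over an assumed range of 0 to 0.10, power at 169 per arm would be 68.0% to 72.5% instead of 80.0%.

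A reader might infer more than the documents support:

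- **That 80% power is not delivered.** The figure is arithmetically right for its inputs, and no document gives the R-squared of the listed covariates. The lower figures are a sensitivity range.
- **That 0.25 was taken from baseline EQ-5D-5L.** A baseline correlation of 0.5 would give this value, but the article does not say where it comes from.
- **That allocation precedes baseline.** Table 4 ticks "Informed consent, enrollment, allocation" at t0, but sections {26a} and {16a} both place randomisation after the baseline assessment, and the t1 column heading itself names randomisation. This is a label slip.

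**What to change.** - **Section {20a}, primary model.** Name baseline EQ-5D-5L as a covariate or, if t1 is a response, constrain the t1 means to be equal across arms. List the factors actually used in randomisation: centre, age group (<81 or ≥81 years) and gender.
- **Section {20a}, secondary models.** Use the baseline score in the same way for HeartQoL, Katz, SPPB, MoCa and HADS.
- **DMP participation.** Stop calling it a stratification factor. Keep it only as an additional covariate recorded before randomisation.
- **Sample size {14}.** State which covariates and what source support R² = 0.25, and show the power if it is lower, as in the table above.
- **Table 4.** Align the allocation tick with sections {26a} and {16a}.

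**Cost.** Wording in the protocol and the analysis plan. Table 4 already schedules EQ-5D-5L and all five secondary scales at t1, so baseline adjustment needs no new data. Whether DMP participation is recorded before randomisation has to be confirmed if it is kept.

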**Inclusion criteria**
Age ≥ 75 years
Planned elective cardiac procedure (OPS: 5–351 to 354, 5-35a, 5–360 to 363)
Sufficient independence, ability to care for self and participate in prehabilitation
Insurance status of all patients from Lower Saxony to patients of AOK (public health insurance provider)
Ability to give consent
Willingness to participate voluntarily in the study after informed consent with signed consent form
Ability to speak, read, and understand German

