## Discussion

PRECOVERY is a randomized controlled multicenter trial with a calculated sample size of 422 participants that aims to examine the long-term efficacy (after 12 months) of a tailored prehabilitation for patients aged 75 years or older undergoing elective cardiac procedures. RCTs focusing on cardiac prehabilitation have shown positive effects in terms of delirium rate, QoL, length of stay in intensive care unit, and improved compliance of postoperative rehabilitation with good safety [69, 70]. Likewise, pre- and postoperative psychological interventions before cardiac surgery additionally led to significant reduction in length of hospital stay and increase in self-efficacy [71, 72]. In the last decade, five reviews with meta-analyses emphasizing on exercise-based prehabilitation prior to elective coronary procedure have been published [12–16] and have shown positive effects as well. In fact, multimodal intervention studies are rare. Mostly, only single-intervention modules were addressed in the context of prehabilitation. Two or three different modules have hardly been conducted. However, it is known from prehabilitation intervention studies with cancer patients that a multimodal prehabilitation approach should include at least physical activity training, nutritional counseling, and psychological support to be effective [73, 74]. In the field of cardiology/cardiac surgery, evidence-based conclusions are lacking—but parallels seem obvious.

The main cohort included in cardiac prehabilitation studies are patients prior to coronary artery bypass graft surgery and/or valvular surgery. To the best of our knowledge, there is currently no evidence proving the effect of a multimodal prehabilitation prior to cardiac intervention such as catheter-based valve reconstructions (e.g., MitraClip, TriClip).

PRÄP-GO [75] and PRECOVERY are the first multicentric prehabilitation trials in Germany focusing on the target to include prehabilitation before elective procedures in older patients into the German healthcare system.

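### The stated covariates do not directly adjust for planned procedure type, which is known before randomisation, and they call DMP participation a stratification factor when it is not a stratum

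*Protocol article*

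**What the plan says.** The section on statistical methods for primary and secondary outcomes {20a} plans a joint model for EQ-5D-5L and states: "Stratification factors of age, sex, participation in DMPs, and center will be included as covariates in the model". HeartQoL is to be analysed in the same way. The mixed linear models for Katz Index, SPPB, MoCa and HADS name the same four covariates again.

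The section on sequence generation {16a} says that randomisation is "stratified by study center, patient age" (below 81 years versus 81 or older) and gender. It mentions neither DMP participation nor procedure type.

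Table 2 lists "Planned elective cardiac procedure" with a range of OPS codes as an inclusion criterion. The objectives give bypass surgery and transcatheter aortic valve replacement as examples. The study setting describes nine recruiting departments of cardiac surgery, cardiology or both. No subgroup analyses are prespecified.

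The Discussion treats the procedures as distinct: earlier studies mainly enrolled bypass and valve-surgery patients, and for the rest "there is currently no evidence proving the effect of a multimodal prehabilitation prior to cardiac intervention such as catheter-based valve reconstructions".

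**The concern.** Open-heart surgery and catheter procedures may well differ in 12-month quality of life and mortality. If they do, a baseline variable available for everyone would explain outcome variance, and leaving it out keeps that variance in the standard error. The design has no spare power: 169 per arm gives 80% only because covariates are credited with an R-squared of 0.25, and the sample size section does not say which covariates those are. A further pre-randomisation predictor would be inexpensive protection.

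The wording on stratification is a separate matter that needs no assumption. Two sections give different lists of strata, and a reader cannot tell whether DMP participation was used in the randomisation.

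**Working it through.** **Inputs from the sample size section {14}:** a "clinically relevant difference of 0.045 points in EQ-5D-5L at t6"; the assumption that "the common standard deviation of the EQ-5D-5L is 0.17"; the assumption that "the observations on the covariates have an R-squared of 0.25"; 169 evaluable patients per arm; two-sided 5% level; 80% power.

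**Step 1. Reproduce the plan's figure.**
- Residual SD = 0.17 × √(1 − 0.25) = 0.1472.
- n per arm = 2 × (1.960 + 0.842)² × 0.1472² / 0.045² ≈ 168.03, rounded up to 169. The exact t calculation also gives 169.
- SE of the difference = 0.1472 × √(2/169) = 0.0160.
- Power = Φ(0.045/0.0160 − 1.960) = 80.2% (80.0% with the t distribution).

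The stated 338 in total is reproduced without procedure type in the model.

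**Step 2. Power if procedure type adds R-squared x beyond the existing covariates.** Residual SD = 0.17 × √(0.75 − x), with 169 per arm. The documents give no value for x, so a range is shown.

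| x (assumed) | Fall in SE | Power at 169 per arm | n per arm for 80% |
|---|---|---|---|
| 0 | 0% | 80.2% | 169 |
| 0.01 | 0.7% | 80.8% | 166 |
| 0.02 | 1.3% | 81.3% | 164 |
| 0.05 | 3.4% | 82.9% | 157 |

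At x = 0.09 the residual SD is 0.17 × √0.66 = 0.1381, the SE is 0.0150, and power is Φ(0.045/0.0150 − 1.960) ≈ 85%.

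**Step 3. What x could be.** For a catheter share p and a mean EQ-5D-5L gap D between procedure types, the variance explained is p(1 − p)D²/0.17². Both p and D are assumptions.

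| p | D | Variance explained | Power |
|---|---|---|---|
| 0.5 | 0.02 | 0.0035 | 80.4% |
| 0.5 | 0.03 | 0.0078 | 80.6% |
| 0.3 | 0.05 | 0.0182 | 81.2% |
| 0.5 | 0.05 | 0.0216 | 81.4% |
| 0.5 | 0.10 | 0.0865 | 84.8% |

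For gaps of 0.05 to 0.10 (p from 0.3 to 0.5), the gain in effective sample size, 0.75/(0.75 − x) − 1, runs from 0.75/0.7318 − 1 = 2.5% to 0.75/0.6635 − 1 = 13%. These are upper bounds for each pair of assumptions, because they credit procedure type with its full marginal share, as if it overlapped with none of the covariates already in the model.

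**Step 4. Chance imbalance.** The SD of the between-arm difference in catheter share is √(p(1 − p) × 2/169), that is 5.0 to 5.4 percentage points for p of 0.3 to 0.5. A 2-SD imbalance with a gap of 0.05 to 0.10 shifts the unadjusted difference by 0.005 to 0.011, which is 0.3 to 0.7 of the SE of 0.0160. That variation is already reflected in the standard error and confidence interval. It is the same loss seen from another side and must not be counted twice.

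**Step 5. Compare the two lists.** Sequence generation: centre, age, gender. Statistical methods, under the label of stratification factors: age, sex, DMP participation, centre. DMP participation is the one item without a counterpart.

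**The case against.** The strongest reply is that a prespecified set made up of the randomisation factors plus one more covariate is valid as it stands. Treatment is allocated independently of procedure type, so the linear EQ-5D-5L comparison is not biased. The sample size reproduces, and power holds at 80% as long as the assumed R-squared is met. All of this stands. A reader might infer from the omission that the estimate is biased, that the trial is underpowered, or that open and catheter patients are pooled with no adjustment at all. The documents support none of these.

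On the last reading, centre is both a stratum and a covariate. Where departments differ in what they do, centre already carries part of the procedure difference. Age is adjusted for, and EQ-5D-5L is measured at baseline in a longitudinal model, which may absorb more. Centre cannot, however, separate procedures within a department that performs both.

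The documents also give no procedure mix and no outcome gap by procedure. The Discussion's remark on catheter-based reconstructions concerns missing evidence for prehabilitation, not prognosis. The size of the gain is therefore open and may be near zero.

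Further details are referred to an analysis plan that is not shown and may add covariates. But the article itself names its covariate set, twice, so that set can be commented on. Finally, open versus catheter is not a ready-made variable: Table 1 contains minimally invasive valve and bypass codes, so a mapping is needed. That is a small cost, not a reason against.

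**Conclusion.** The point holds as an inexpensive improvement, not as an error in the design. The stated covariates leave out direct adjustment for a pre-randomisation fact in a trial that mixes open and catheter procedures. What is forgone is precision of unknown size: about 0 to 5 points of power at 169 per arm if the added R-squared is 0 to 0.09, with the low end plausible after centre. For the survival part, an omitted prognostic factor could matter more, but the article gives no mortality inputs from which to quantify it.

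The conflict over DMP participation rests on no assumption. The two sections name different stratification factors and must be reconciled.

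**What to change.** Before unblinding:

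1. Add planned procedure type (open surgery versus catheter) as a covariate in the joint model for EQ-5D-5L and survival, in the analogous HeartQoL model and in the secondary mixed linear models. Define it by a prespecified mapping of the OPS code planned at inclusion, not by the procedure actually performed, which is determined after randomisation. Confirm that the planned code is recorded for each patient before randomisation.
2. Leave the randomisation strata as they are.
3. State the stratification factors as centre, age (below 81 versus 81 or older) and gender. List DMP participation as an ordinary baseline covariate, unless it was in fact a stratum, in which case correct the section on sequence generation.

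The cost is one model degree of freedom, the code mapping and a few lines of text. In the survival part, the treatment effect becomes conditional on procedure type as well, so its meaning changes slightly. If the change is made only after results by arm are known, it would be open to challenge as data-driven.
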